**Figure 3 F3:**
[figure not shown]
Figure depicting how telemedicine characteristics are collected at the hospital level and at the individual patient level. It clarifies the source of the collected clinical content used for the subgroup analyses rather than the type of data source.

### Data collection and quality control

Data of the HF registry will be remotely monitored for major outliers and missing variables using the NHR; these processes have been described elsewhere.^30 35^ The NHR uses a unique individual patient identifier (NHRpersonID) to deduplicate registrations of the same patient (at the same or different hospitals) in the HF registry.^36^ During the RELEASE-HF study, researchers will perform an additional check on completed data and provide assistance to hospitals to reduce missing values, as well as assistance to reduce registration burden.

Telemedicine interviews, using an interview guide with closed-ended questions, will be performed by a RELEASE-HF investigator and conducted with clinicians (eg, cardiologist, HF nurse, nurse specialist, physician assistant). Interviews will be held during the 36-month period of data collection. All hospitals with telemedicine in HF care will be interviewed once, and the data will be checked with the hospitals once during the data collection period to be aware of changes in the components and status of telemedicine. For each hospital, the 6-monthly costs of telemedicine are determined via interviews and registration data (if at hand). The units will be linked to the unit cost guideline provided by the Dutch National Health Care Institute (Dutch: Zorginstituut Nederland).^37^ These interviews will be performed by a health technology assessment (HTA) scientist and conducted with clinicians or finance department staff. All participants will provide informed consent.

Patient-level telemedicine data are collected by a clinician, data manager or researcher at the hospital where the patient is being treated because these individuals have access to the identification log of the HF registry. Collected data will include the start date of telemedicine use and the frequency at which measurements are sent to the treating hospital, with a high rate typically referred to as a high-intensity (or acute) protocol and a low rate as a low-intensity (or stable) protocol.

The Heart4Data consortium will establish opportunities for data linkage between the HF registry and other national registry databases, in collaboration with public partners (figure 2).^28^ At the time of writing, a collaboration between these databases and the HF registry is not yet established for all external national databases.

### Statistical analysis

#### Clinical effectiveness

Descriptives are presented for all variables of the HF registry and telemedicine components. We will present the number of days without unplanned hospitalisation for HF during 365 days after baseline, the average duration of unplanned HF-related hospital stays, the number of deaths and the time until death.

##### Preparation of the statistical model

As a first step, we describe how the overall effect of offering any type of telemedicine versus not offering telemedicine will be estimated. This analysis will subsequently be used for a comparison of telemedicine effects on days alive without unplanned HF-related hospitalisation during 1 year across subgroups.

The cohort is restricted to individuals with newly diagnosed HF, that is, at most 3 months prior to baseline. The exposure contrast is defined as offering any type of telemedicine after first presentation with HF at the hospital outpatient clinic versus patients not offered telemedicine. The telemedicine status for the entire follow-up is defined by 6 months after baseline measurement of telemedicine, used as an observational analogue of an ‘intention to treat’ analysis in which the stopping of telemedicine is disregarded.

Because telemedicine administration is dependent on patient characteristics, confounding by indication will be accounted for. Based on clinical consensus, the following patient-level confounding variables measured at baseline will be adjusted for: age, sex, SES, BMI, NYHA, LVEF, aetiology of HF, systolic blood pressure, diastolic blood pressure, heart rhythm, heart rate, chronic respiratory disorders, OSAS, stroke, extra cardiac arterial vascular pathology, DM, hypertension, anaemia, CKD, malignancy, heart rhythm disorders, depression and thyroid disease (see table 3 and online supplemental material 1).

The primary outcome model is a linear mixed model with a random intercept for the participating centre and is specified as follows. The outcome is measured in days, and because the final measurement may be less or more than 365 days after baseline, we rescale the number of days of unplanned hospitalisation to the number of days under follow-up to 365 days. The outcome is computed by subtracting the days of unplanned hospitalisation or death from 365. The earlier described confounding variables are added to the primary outcome model to adjust for confounding. Continuous covariates are modelled using splines. Multicollinearity between confounding variables and the telemedicine status is evaluated. The coefficient for telemedicine in the primary outcome model represents the average treatment effect of offering any telemedicine within 3 months after HF diagnosis compared with not offering telemedicine on days with unplanned HF-related hospitalisation during a year in the population of patients with newly diagnosed HF. Robust SEs are estimated to compute CIs.

For the secondary outcome functional status, a similar approach is taken to estimate the average treatment effect of offering any telemedicine within 3 months after HF diagnosis compared with not offering telemedicine on functional status after 1 year in the population of patients with newly diagnosed HF. For this analysis, the outcome model is a multinomial regression model, and baseline functional status is added as a covariate. The risk difference relative to the reference outcome category is assessed using the predicted outcomes of the primary outcome model offering of telemedicine versus not offering, to obtain the marginal risk difference.^38–40^ Similarly, for the secondary outcomes health status and hrQoL, the outcome model is a probit regression model, with baseline measurements added as a covariate. Healthcare utilisation will be assessed using a Poisson regression model, and all-cause mortality will be assessed using binary logistic regression.

We plan to perform the following additional analyses. First, we plan to perform the analysis with the start of follow-up defined at the T1 (after 6 months) measurement and the outcome of unplanned hospitalisation days during 6 months. This is because telemedicine status can be misclassified when it is started shortly after baseline but is not registered in the data. Second, we plan to perform a per-protocol analysis of telemedicine use if detailed information on starting and stopping of telemedicine is available through linkage. Finally, we plan to perform all analyses in the entire cohort, rather than the cohort restricted on HF diagnosis, to a maximum of 3 months prior to T0 (baseline).

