### Outcome measures

#### Primary outcome

The number of days alive without unplanned hospitalisation within 1 year of follow-up is derived from the number of unplanned hospital days as collected in the HF registry (table 1).

**Table 1 T1:** Operationalisation of exposure variable and study outcomes

Variable	Source	Time of collection	Operationalisation
Exposure			
Telemedicine	HF registry, telemedicine-generated data	T0, T1*, T2	Whether a patient receives telemedicine. Five categories: (1) no telemonitoring†; (2) telemonitoring by telephone; (3) telemonitoring, non-invasive based on traditional parameters (eg, blood pressure, ECG); (4) telemonitoring using ICD based on HF parameters; and (5) telemonitoring, invasive using sensors in the bloodstream or heart.
Primary outcome			
Number of days spent alive without unplanned hospitalisations within 1 year of follow-up	HF registry	T1*, T2	Number of days directly related to unplanned cardiac hospital admission due to HF. Number of admission days will be summed up over a period between follow-up moments and subtracted from 365 days.
Secondary outcomes			
Costs	Derived from HF registry, external data source, EHR, interviews	T0, T1*, T2	Costs estimated from patient, disease and treatment characteristics. Information taken into account includes medication use, whether the patient underwent cardiac interventions (eg, pacemaker implantation, percutaneous coronary intervention), use of telemedicine, hospital admission days, visits to the outpatient clinic, visits to the emergency room, admission days at an intensive care unit and visits to the GP related to HF.
All-cause mortality	HF registry, external data source	T1*, T2	Mortality status, determined after verification at the Personal Records Database (in Dutch: Basisregistratie Personen). Mortality is independent of HF (all-cause).
Functional status	HF registry	T0, T1*, T2	NYHA classification: a functional classification of patients based on severity of symptoms and physical activity, with specific attention to fatigue, palpitation and dyspnoea. Scores are linked to one of four NYHA classes: class I: no limitation; class II: slight limitation; class III: marked limitation; and class IV: unable to carry on any physical activity without discomfort.^1^

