### Exposure measurement

Exposure to telemedicine is measured in the HF registry at 6 months and 12 months of follow-up as non-use of telemedicine, telephone only, non-invasive telemedicine, implantable cardioverter defibrillator-based telemedicine or invasive telemedicine (table 1). Telemedicine output can be different from the closed-ended interviews that correspond to all outpatient clinic contacts in general. The components of the telemedicine intervention will be assessed at the hospital level at one time during the follow-up period. Table 2 provides an overview and operationalisation of the main components of the telemedicine intervention that have been described in existing literature or at the local (eg, hospital) level.^7 32–34^ The components will be validated and possibly further refined based on the interviews. Figure 3 illustrates the flow of data collected at the hospital level and at the patient level.

**Table 2 T2:** Overview and operationalisation of telemedicine variables collected in the qualitative study

Component	Definition	Operationalisation (examples)
Supplier	(External) supplier of telemedicine for patients with HF.	Sanacoach, Luscii, Motiva/Philips, linked in personal environment in EHR.
Purpose of telemedicine	The intention/motives for which the telemedicine intervention is administered: patient level and/or hospital level.	Monitoring, prevent exacerbation, reduce workload, reduce costs, patient-centred care.
Considering telemedicine	First time a clinician considered telemedicine in HF management.	After diagnosis, (re)hospitalisation, titration phase.
Structured telephone support	Structured monitoring by telephone without using applications or devices specific to telemedicine and monitoring HF.	Present or not present.
Applications	Technologies or platforms on which the patient could receive telemedicine.	Smartphone, tablet, laptop, television, smartwatch.
Devices	Accessory a patient could use to perform telemedicine.	Blood pressure device (with or without Bluetooth), weight scale (with or without Bluetooth), smartwatch.
Involved healthcare workers	Involved healthcare workers and their role in considering and executing telemedicine.	HF nurse, nurse specialist, cardiologist.
Control centrum	The presence or absence of a control centrum to check the submitted measurements and questions.	Present or not present.

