##### Research question 2: effectiveness of different telemedicine components

Research question 2 investigates the effectiveness of the different forms of telemedicine intervention. We assess this question by performing three separate analyses in which intervention aspects are contrasted in the subset of participants that received telemedicine. The presence or absence of a telemedicine component is determined at a hospital level. The components of telemedicine that are contrasted are presence versus absence of a service centre, presence versus absence of an educational module, and high-intensity versus low-intensity protocol (table 2).

The population of interest is patients with newly diagnosed HF (maximum 3 months prior to baseline) who received telemedicine. Offering of telemedicine is measured at 6 months after baseline.

In addition to the set of confounding variables at the patient level used in the analysis above, confounding variables at the hospital level are considered because indication for telemedicine is expected to differ across hospitals. Confounding variables include academic or non-academic hospital, presence of a specialised heart centre, presence of an outpatient ward, size of outpatient ward (number of patients/year), staffing of the HF outpatient clinic and full-time equivalent of outpatient-ward staff.

For each of the three contrasts, the primary outcome model is fitted to estimate the average treatment effect of a component relative to the corresponding reference component on days of unplanned hospitalisation during 1 year in the population of patients with newly diagnosed HF that initiated telemedicine.

The secondary outcomes functional status, health status and hrQoL are assessed using similar approaches but using multinomial, probit and probit regression model, respectively. Healthcare utilisation and all-cause mortality will be assessed using Poisson regression model and binary logistic regression, respectively.

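### The primary effect is declared as that of offering telemedicine, but the data record only receipt, so it can be reported only as use versus non-use

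*Protocol article*

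**What the plan says.** In the protocol article, under Preparation of the statistical model, the contrast is "defined as offering any type of telemedicine after first presentation with HF at the hospital outpatient clinic versus patients not offered telemedicine". The coefficient "represents the average treatment effect of offering any telemedicine within 3 months after HF diagnosis compared with not offering telemedicine", and the Abstract describes the main comparison in the same terms. Status is fixed once: "The telemedicine status for the entire follow-up is defined by 6 months after baseline measurement of telemedicine". The article presents this as the observational counterpart of intention to treat, "in which the stopping of telemedicine is disregarded".

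The data item is described elsewhere:

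- Table 1 operationalises it as "Whether a patient receives telemedicine", in five categories: no telemonitoring, and four types of telemonitoring.
- Exposure measurement says: "Exposure to telemedicine is measured in the HF registry at 6 months and 12 months of follow-up as non-use of telemedicine", followed by the types of use.
- Data collection and quality control adds, at patient level: "Collected data will include the start date of telemedicine use", plus how often measurements are sent.
- Research question 2 says: "Offering of telemedicine is measured at 6 months after baseline". The same section describes these patients as having received telemedicine.
- The Cost-effectiveness section and Research question 3 compare those who use telemedicine with those who do not.

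**The concern.** Offering and receiving are different exposures. An offer is made by the hospital or clinician, while receipt also depends on whether the patient accepts. An intention-to-treat analogue keeps people who decline in the offered group. With a variable that records only receipt, they move to the comparison group.

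Two things are at stake. First, the result would be published as the effect of a policy (offering) that the study did not measure, and that is the result a hospital or payer would act on. Second, the contrast carries patient self-selection. The adjustment list has partial proxies for take-up, such as age, SES, NYHA class, stroke and depression. It has nothing on cognition, frailty, digital skill or motivation.

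**Working it through.** **Step 1. Set the declared contrast beside the recorded item.**

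| Patient | Declared contrast | Recorded at 6 months |
|---|---|---|
| Never offered | not offered | non-use |
| Offered, declined | offered | non-use |
| Started, stopped before 6 months | offered | non-use if the item means current use; a type of use if it means any use since baseline |
| Using at 6 months | offered | a type of use |

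The second row is misplaced under any reading of the item, and would be at any other visit. The third row is misplaced only under the current-use reading. The start date and measurement frequency exist only for patients who started, so they cannot separate row 1 from row 2.

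**Step 2. See whether a planned additional analysis recovers the offer.** Three are listed under Preparation of the statistical model: restarting follow-up at 6 months, a per-protocol analysis if linkage gives start and stop data, and dropping the restriction to recent diagnosis. None identifies who was offered. The misclassification acknowledged there concerns telemedicine started shortly after baseline and not registered.

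**Step 3. Illustrate the size.** The article gives no share offered, uptake or stopping rate, so these inputs are assumptions. The value of use is set at the 6.4 days (SD 21.1) of the Sample size calculation.

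That calculation reproduces. Per group, 2 × (1.960 + 0.842)² × 21.1² / 6.4² rounds up to 171, or 342 in total, and 342 / 0.80 = 428 after rounding up. A t-based version gives 430. The stated figure is 432. This neither supports nor weakens the point.

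Let u be uptake among those offered, and let decliners gain nothing. Effect of offering = u × 6.4 + (1 − u) × 0:

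- u = 0.8: 5.12 days; 6.4 / 5.12 = 1.25
- u = 0.6: 3.84 days; 6.4 / 3.84 = 1.67
- u = 0.5: 3.20 days; 6.4 / 3.20 = 2.00

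With no prognostic selection, the use contrast stays at 6.4 days. Calling it the effect of offering would then overstate that effect by 25% at 80% uptake and by 100% at 50%.

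Let o be the share offered. Decliners make up o(1 − u) / [o(1 − u) + (1 − o)] of the reference group:

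- o = 0.5: 0.10 / 0.60 = 16.7% at 80% uptake; 0.25 / 0.75 = 33.3% at 50%
- o = 0.3: 7.9% and 17.6%
- o = 0.7: 31.8% and 53.8%

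**Step 4. Add self-selection.** Suppose decliners' untreated outcome differs from users' by s days, unadjusted, while offered and never-offered patients have the same average prognosis (set to 0). Users' untreated mean is then r = −(1 − u)s. With w the decliner share from step 3, the use contrast is (r + 6.4) − w(r + s). At o = 0.5 and u = 0.8:

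- s = −5: (1 + 6.4) − 0.167 × (−4) = 8.07 days
- s = +5: (−1 + 6.4) − 0.167 × 4 = 4.73 days

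The effect of offering is 5.12 days in both cases. The gap can therefore go either way, and its direction is not known from the article.

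**The case against.** The strongest reply is that offering was meant loosely, as providing. On that reading the model is a sound comparison of users with non-users, and rewording changes no coefficient. Adjustment is extensive, and the Discussion concedes that confounding cannot be fully avoided. This holds as far as it goes: once labelled correctly, the comparison is interpretable. It does not rescue the text, because the intention-to-treat description and the stated meaning of the coefficient would still be wrong. The Discussion also names selection by physicians and nurses, not by patients.

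A reader might infer four stronger things that the article does not support:

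- **Early stoppers are certainly coded as not offered.** The article does not say whether the 6-month item means current use or any use since baseline, and the data dictionary is in a supplement that is not shown. Under the second meaning, early stoppers count as exposed, as the plan intends.
- **The component analyses are contaminated too.** Research question 2 compares components among recipients only, so decliners cannot enter a reference arm. Only one sentence there needs aligning.
- **The bias rivals the 3.2–3.8 day interaction the study is sized for.** A bias in the main effect reaches an interaction only if it differs between subgroups, and nothing in the article shows that it does. Any such figure would also rest on invented rates of offer, uptake and prognosis.
- **A true offer analysis could be run on data already planned.** Data collection and quality control describes one interview and one check, for hospitals with telemedicine. It promises no dated history of availability, and no interview for hospitals without telemedicine. Clinicians also select patients within centres, so centre availability is not a patient-level offer.

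**Conclusion.** The mismatch is real and stands on the article's own text: the declared effect is of offering, the recorded exposure is receipt, and nothing described records an offer or a refusal. Decliners are analysed as not offered. The coefficient estimates use versus non-use with partly unadjusted self-selection, and cannot be reported as an effect of offering. The decliner part does not depend on when exposure is read. The stopper part does, and is conditional on the 6-month item meaning current use.

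The size cannot be computed from the article. The figures of 5.1 days at 80% uptake and 3.2 days at 50%, against 6.4 days for use, assume that decliners gain nothing. They show that the two effects are not interchangeable, but do not estimate the error in this study.

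**What to change.** 1. In the Abstract and in Preparation of the statistical model, restate the contrast and the coefficient as receiving (using) versus not receiving telemedicine, and drop the intention-to-treat description. Align the Research question 2 sentence that says offering is measured at 6 months. Limit conclusions to use, which also brings the clinical analyses into line with the cost-effectiveness sections.
2. State whether the 6-month item means current use or any use since baseline. If current, use the patient-level start date, where available, to code patients who started and stopped before 6 months as exposed, so that stopping really is disregarded.
3. Optionally, if dated centre-level availability can be obtained, including for hospitals without telemedicine, add a sensitivity analysis by centre availability. Label it as that, and note the extra data needed, the lower precision and the confounding between hospitals.

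Item 1 is wording only. Item 2 uses data already planned, where they exist. Item 3 needs extra collection. The downside is that the main claim narrows from offering to use.

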## Methods and analysis

### Study design

RELEASE-HF is a nationwide, observational, registry-based cohort study across multiple hospitals in the Netherlands.^27^ The study collects routine data longitudinally. We record the health status of and cardiac interventions in patients with HF and simultaneously observe the natural (de)implementation of telemedicine. RELEASE-HF is linked to the Heart4Data consortium which started in 2022 to create a national and sustainable infrastructure for cardiovascular registry-based research in the Netherlands.^28^ This infrastructure will develop a framework for the governance, ethical, legal, financial, information technology and methodological factors necessary for registry-based research.

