#### HF registry

The HF registry is an ongoing quality registry in the Netherlands facilitated by the NHR, a non-profit organisation that aims to contribute to quality improvement and safety in cardiac care.^29 30^ The HF registry serves as an ongoing learning healthcare system through benchmarking and quality control. Since 2019, it has been introduced as a voluntary, nationwide HF registration. Patient data are collected non-consecutively, and for the registry no informed consent is asked. Data of included patients are collected at three timepoints: at baseline, 6 months and 12 months from the time since diagnosis. The HF registry includes variables on three levels defined in a data dictionary: patient characteristics, treatment characteristics and clinically relevant outcomes. The data dictionary is a dynamic document (ie, the included variables and definitions may change over time) because it is based on current HF guidelines and compiled by a committee consisting of delegated cardiologists from Dutch hospitals. A detailed up-to-date data dictionary with an overview of the variables collected within the HF registry is always published on the NHR website. Online supplemental material 1 provides an overview of the data dictionary of the HF registry, September 2022 version; the content is subject to change.^31^

10.1136/bmjopen-2023-078021.supp1Supplementary data

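### The adjustment set omits baseline HF therapy, cardiac devices and inclusion date, so differences in background care can be credited to telemedicine

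*Protocol article*

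**What the plan says.** The section on preparing the statistical model names the adjustment set in full. It opens with "Based on clinical consensus, the following patient-level confounding variables measured at baseline will be adjusted for: age, sex, SES, BMI, NYHA, LVEF", runs through aetiology, blood pressure, heart rhythm, heart rate and comorbidities, and closes with "anaemia, CKD, malignancy, heart rhythm disorders, depression and thyroid disease". The model is "a linear mixed model with a random intercept for the participating centre", and "The earlier described confounding variables are added to the primary outcome model to adjust for confounding". The additional analyses listed next change the start of follow-up, the exposure definition and the cohort, but not the covariates. Research question 2 adds hospital-level variables (academic status, heart centre, clinic size, staffing). None of them is therapy or time.

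Elsewhere the article describes what is recorded and when telemedicine is used:
- HF registry: "The HF registry includes variables on three levels defined in a data dictionary: patient characteristics, treatment characteristics and clinically relevant outcomes", with data collection at baseline, 6 and 12 months.
- Table 1, costs (T0, T1, T2): "Information taken into account includes medication use, whether the patient underwent cardiac interventions (eg, pacemaker implantation, percutaneous coronary intervention" and further items.
- Table 1, exposure: one category of telemedicine is telemonitoring through an ICD.
- Table 2, examples of when a clinician first considers telemedicine: "After diagnosis, (re)hospitalisation, titration phase".
- Study design: the study will "simultaneously observe the natural (de)implementation of telemedicine". It started in June 2021 and lasts 4 years, and hospitals may join later.
- Cost-effectiveness: hospitals have been able to claim telemedicine costs since 2023.

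**The concern.** A confounder here is anything that affects both who is offered telemedicine and the days lost to HF admission or death. The document itself gives reason to think that treatment and time do both.

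The Introduction says optimised guideline-directed therapy may reduce HF morbidity. A patient needs an ICD to be in the ICD-based exposure category, so device status bears directly on exposure. The reimbursement change and the observed (de)implementation mean that the chance of being offered telemedicine depends on the date of inclusion. The registry's data dictionary is revised with current HF guidelines, so standards of care are also expected to move.

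The plan costs medication and cardiac interventions but does not use them to make the groups comparable. A centre intercept deals, in part, with stable differences between hospitals. It does nothing about two patients in the same hospital on different therapy, or about one hospital in its first and third year. The same patient-level list feeds the main effect, the subgroup analyses and the component contrasts.

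**Working it through.** **1. The plan's own yardsticks.** The sample size section gives a 6.4-day effect, SD 21.1, 5% type I error, 80% power and 20% dropout. Per arm (two-sided): 2 × (1.96 + 0.84)² × 21.1² / 6.4² ≈ 2 × 7.85 × 445.21 / 40.96 ≈ 171. That is 342 in total, and 342/0.8 ≈ 428. The t-test version gives 172 per arm, and 344/0.8 = 430. The plan states 432, which reproduces closely. Then 432 × 12 = 5184 and 5184/0.8 = 6480. These figures are not in dispute. The 6.4 days and the 3.2-day interaction target serve below only as scale.

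**2. The list.** Counted item by item it has 23 entries: 4 demographic (age, sex, SES, BMI), 3 on HF severity and cause (NYHA, LVEF, aetiology), 4 haemodynamic or rhythm measures, and 12 comorbidities. Drugs: 0. Devices: 0. Dates: 0.

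**3. Omitted therapy.** Bias ≈ (difference in prevalence between groups) × (effect of the omitted factor given the listed covariates). The document gives neither input, so both are assumed:
- Low: 0.15 × 5 days = 0.75 days; 0.75/6.4 = 12%.
- High: 0.30 × 10 days = 3.0 days; 3.0/6.4 = 47%.
- Wider inputs (0.10 × 3 to 0.40 × 15) give 0.3 to 6.0 days, which shows how far the answer depends on the assumptions.

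**4. Subgroup contrasts.** The bias in a contrast is the bias in subgroup A minus the bias in subgroup B. If both carry 3.0 days, it is 3.0 − 3.0 = 0. If the imbalance is 30 points in one and 15 in the other with a 10-day effect, it is 3.0 − 1.5 = 1.5 days, or 1.5/3.2 = 47% of the interaction target. That second case is again an assumption.

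**5. Omitted calendar time.** A small simulation used 29 centres of 179 patients and a roll-out date spread evenly over 3 years. The probability of telemedicine was 5% before roll-out and 70% after. Centre SD was 3, residual SD 21.1 and the true effect 0, with 20 runs per row.

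| Assumed outcome trend (days/year) | Estimated effect, no time term | With time term |
|---|---|---|
| 1 | 0.59 | −0.28 |
| 2 | 1.45 | 0.08 |
| 4 | 3.08 | −0.18 |

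With 20 runs the entries are good to a few tenths of a day. The random intercept alone did not remove the trend; the time term did.

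**6. Against precision.** With 5184 patients split equally and clustering ignored, the 95% half-width is 1.96 × 21.1 × 2/√5184 = 1.96 × 21.1 × 2/72 ≈ 1.15 days. A bias of 1.5 to 3 days would exceed it; 0.75 days would not. The restriction to newly diagnosed patients may leave fewer than 5184 and so widen the interval.

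**The case against.** The strongest reply is that the bias is asserted rather than shown. No therapy imbalance, therapy effect or time trend is documented, and an effect of 5–10 days is 78–156% of the whole planned telemedicine effect. This stands: the figures are illustrations only.

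NYHA, LVEF, aetiology, blood pressure, heart rate and CKD may stand in for part of the treatment difference. The limit of 3 months since diagnosis narrows treatment history, and the hospital-level variables in research question 2 partly reflect background care. This also stands, and it shrinks the problem. But none of these carries calendar time, and the planned analysis of the entire cohort lifts the 3-month limit.

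On time, (de)implementation can go either way. If the 36 months of data collection include the 12-month follow-up, inclusion spans only about 24 months, against the 3 years simulated. That affects size, not the fact that date is absent.

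On measurement, the data dictionary is in a supplement that is not shown, the cost row mixes several sources, and diuretic class is sought through linkage that is not yet secured. T0 may fall up to 3 months after diagnosis, so T0 therapy may already reflect telemedicine. Both points stand and shape the remedy.

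Finally, the list rests on clinical consensus and the Discussion concedes residual confounding. Conceding it in general does not explain why these particular factors were left out.

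Three stronger readings are tempting and unsupported. A reader might infer that telemedicine is tied to titration, but Table 2 lists that phase only as one example. A reader might set the 3.0-day bias against the 3.2-day interaction target and conclude that the subgroup findings are nearly all bias, but a bias common to both subgroups cancels. A reader might infer that telemedicine will be flattered, but patients still being titrated may be less treated and patients in active programmes better treated, so the sign is open.

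**Conclusion.** The point holds as a gap in a stated adjustment set. Because the article names the covariates and says that they are what enters the model, this is not detail left to an analysis plan. Baseline therapy, device status and inclusion date are plausible confounders on the document's own account, and the centre intercept does not cover them. Differences in background care can therefore be credited to telemedicine.

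Under the stated assumptions the bias in the main effect is 0.75–3.0 days, or 12–47% of 6.4 days. Omitted calendar time alone gives about 0.6–3.1 days for assumed trends of 1–4 days a year. Neither range is an estimate for this study. Subgroup contrasts suffer only where the bias differs between subgroups. The omission should be corrected before analysis; it does not invalidate the design or change the sample size.

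**What to change.** Extend the list in the section on preparing the statistical model, for all outcome models including the component models, with:
- (a) date of inclusion, as a spline;
- (b) baseline HF drug classes, as far as the registry records them;
- (c) baseline ICD, CRT or pacemaker status.

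Use values recorded at T0 and before telemedicine starts, so that treatment changes brought about by telemedicine are not adjusted away. The plan already collects a patient-level telemedicine start date, which can identify early starters. For patients already on telemedicine at T0, report results with and without the therapy terms, because T0 therapy may then be a mediator. Check that device carriers include enough patients without telemedicine to support the comparison. If any of the three is left out on purpose, state the reason.

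The cost is a few degrees of freedom in a cohort of thousands and some extra missing values. Drug detail that depends on linkage, such as diuretic class, may be unavailable. Inclusion date does not depend on that linkage and should be added in any case.
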